### Data Collection Procedures

Participants will be enrolled in the study and assigned a unique ID number, which will be used for randomization using the mobile app. Once the participant has been randomly assigned, baseline measurements and tracking information will be collected and recorded using the Open Data Kit (ODK) platform (Get ODK Inc) and directly uploaded to the server. Data will be collected on age, sex, occupation, date when identified as a person with presumed TB, distance to the health facility of enrollment, test method used (ie, sputum smear microscopy or Xpert MTB/RIF), and knowledge and perceptions about the disease and treatment. We will train outcome assessors to objectively conduct interviews and assess outcomes at follow-up. This approach will minimize any biases associated with the team administering the intervention.

### Trial End Points, Outcomes, and Timelines

The primary end point for the trial is completion of the TB diagnosis process within 30 days of being recruited. Completion of TB diagnosis will be defined as submitting a sputum sample for Xpert MTB/RIF testing and receiving test results within 30 days of being identified as a person with presumed TB. The 30-day follow-up period was selected based on previous studies for comparison [25,33]. Completion of TB diagnosis will be measured as the proportion of patients who completed TB diagnosis within 30 days out of all persons with presumed TB recruited into the study.

The secondary outcomes will include (1) TB treatment initiation, which will be defined as starting TB treatment within 30 days of being diagnosed (this will be measured as the proportion of patients diagnosed with TB who initiated treatment out of the total number of patients diagnosed with TB recruited into the study); (2) median turnaround times for TB diagnosis and treatment initiation; and (3) acceptability and feasibility of the study interventions. The detailed procedures and timelines are indicated in Table 1.

**Table 1. T1:** Study procedures and timelines.

Study procedure	Screening	Baseline	Day 0	Results available	Day after results reminder	Day 30
Enrollment						
Eligibility screening	✔					
Informed consent	✔					
Allocation	✔					
Sociodemographic information		✔				
Clinical history		✔				
Knowledge of and attitudes regarding TB^a^		✔				
Interventions						
SMS reminders			✔	✔	✔	
Telephone calls			✔	✔	✔	
Transport incentives				✔		
Assessments						
Sputum submission						✔
Receipt of results						✔
Receipt of interventions						✔
Treatment initiation for those diagnosed						✔
Acceptability assessment						✔
Qualitative study on perceptions and experiences of the interventions						✔

a TB: tuberculosis.

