**Methods:**

This will be a 5-arm individual randomized controlled trial among persons with presumed TB aged 18 years or older who are referred for Xpert MTB/RIF testing. Participants will be randomly assigned (2:2:2:1:1) to (1) standard of care, (2) SMS reminders only, (3) telephone calls only, (4) SMS reminders and a transport incentive, and (5) telephone calls and a transport incentive. An estimated sample size of 2389 participants will be considered. The primary outcome will be completion of TB diagnosis, defined as submitting a sputum sample for Xpert MTB/RIF testing and receiving test results within 30 days of being identified as having presumptive TB. The secondary outcomes will include (1) TB treatment initiation, which will be defined as starting TB treatment within 30 days of being diagnosed; (2) median turnaround times for TB diagnosis and treatment initiation; and (3) acceptability and feasibility of the interventions. Participants will be followed for 30 days to check whether they have tested for TB and collected their results. Chi-square tests will be performed for categorical outcomes. Analysis will be by intention to treat. Modified Poisson regression models will be used to estimate the effects of the interventions on completion of TB diagnosis and treatment initiation.

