### Study Population

The study population will comprise persons with presumed TB who did not complete diagnosis on the same day as their health facility visit. Persons with presumed TB will be defined as those presenting with signs and symptoms suggestive of TB, including cough, fever, night sweats, and unexplained weight loss.

We will include (1) patients referred for Xpert MTB/RIF testing; (2) those aged 18 years or older; (3) those currently residing in the health facility’s catchment area; (4) those willing to consent to the study procedures, including follow-ups, and able to sign an informed consent form; (5) those who own a mobile phone and have it in their possession on the day of recruitment; and (6) those able to read (a test SMS text message will be sent to the patient’s mobile phone, and they will be asked to read it aloud). Participants planning to move out of the study area within 3 months after enrollment and those participating in other related studies (eg, those involving SMS reminders, telephone calls, or transport incentives) will be excluded.

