### Participant Follow-Up Procedures

Follow-up interviews will be conducted after 30 days from the day of recruitment for all participants primarily through face to face interviews at the health facility. Home visits will be conducted for patients who fail to turn up at the health facility. If still we can not access the patient, telephone calls will be made by research assistants to conduct the interview over the phone. At follow-up, data will be collected on whether the TB tests had been performed, along with the date of the TB test results, the date of registration for TB treatment, and the TB registration number. If a participant does not submit a sputum sample, receive test results, or initiate treatment after diagnosis, they will be asked to provide reasons for not undergoing testing, receiving results, or starting treatment.

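### Treatment initiation is defined over 30 days from diagnosis but assessed only at 30 days from recruitment, so part of the window goes unobserved, by an amount that may differ between arms

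*Protocol article*

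**What the plan says.** Two clocks are in use.

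- **The outcome clock starts at diagnosis.** Under Trial End Points, Outcomes, and Timelines, the first secondary outcome is "TB treatment initiation, which will be defined as starting TB treatment within 30 days of being diagnosed". The stated measure is "the proportion of patients diagnosed with TB who initiated treatment out of the total number of patients diagnosed with TB recruited into the study".
- **The observation clock starts at recruitment.** Participant Follow-Up Procedures says "Follow-up interviews will be conducted after 30 days from the day of recruitment for all participants". The abstract's Methods says "Participants will be followed for 30 days to check whether they have tested for TB and collected their results". The end points section adds that "The 30-day follow-up period was selected based on previous studies for comparison". In Table 1 the row "Treatment initiation for those diagnosed" is ticked under Day 30 only, and Day 30 is the last column.

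Two further statements matter. Study Population enrols "persons with presumed TB who did not complete diagnosis on the same day as their health facility visit", so receipt of results comes after the visit day. At the follow-up contact the team collects "the date of the TB test results, the date of registration for TB treatment, and the TB registration number". The article describes no later contact or register check for participants who are diagnosed.

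**The concern.** The outcome needs 30 days of observation after diagnosis, and the schedule provides 30 days after recruitment. The shortfall equals the time from recruitment to diagnosis. That time is unlikely to be the same in every arm: the interventions exist to get people through the diagnostic process, and turnaround time to diagnosis is itself a secondary outcome. A difference in observed treatment initiation could then arise from unequal observation alone. Blinded outcome assessors and analysis by intention to treat do not remove this.

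At stake is the first-listed secondary outcome, which Objectives and Hypothesis also places within the primary objective. The primary end point (completion of diagnosis within 30 days) is not touched. The matter cannot be left to an analysis plan, because starts that were never looked for cannot be recovered at analysis.

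**Working it through.** **Observed window.** With diagnosis on day d after recruitment and assessment on day 30, the observed window is 30 − d days out of the 30 defined.

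| Day of diagnosis | Days observed | Share of defined window |
|---|---|---|
| 1 | 29 | 97% |
| 7 | 23 | 77% |
| 14 | 16 | 53% |
| 21 | 9 | 30% |
| 30 | 0 | 0% |

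A day-30 diagnosis still counts as a success for the primary end point and still enters the denominator for treatment initiation.

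**Possible size.** The plan has no figure to reproduce here. The Introduction cites 19% pretreatment loss to follow-up, so I take 81% started by 30 days after diagnosis, identical in both arms. Any gap is then an artefact. The diagnosis days and the delay distributions are my assumptions, since the article gives neither.

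- *Constant hazard:* λ = −ln(0.19)/30 = 0.0554 per day, and observed initiation = 1 − exp(−λ(30 − d)). This gives 74.9% for d = 5, 72.0% for d = 7, 58.8% for d = 14 and 42.5% for d = 20.
- *Starts concentrated soon after diagnosis:* observed initiation = 0.81 × (1 − exp(−(30 − d)/m)) / (1 − exp(−30/m)), with a mean delay m of about 2, 5 or 10 days.

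Spurious gap, intervention minus control, in percentage points:

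| Diagnosis day, control vs intervention | m = 2 | m = 5 | m = 10 | Constant hazard |
|---|---|---|---|---|
| 7 vs 5 | 0.0 | 0.3 | 1.5 | 2.9 |
| 14 vs 5 | 0.0 | 2.8 | 10.2 | 16.2 |
| 20 vs 7 | 0.5 | 10.2 | 22.8 | 29.5 |

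With 95% started by 30 days and a constant hazard, the three gaps are 1.8, 12.0 and 26.8 points.

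**Direction.** The table assumes that the arms differ only in speed. The sample-size hypothesis is about more people completing: loss before diagnosis falls from 24% to 14.4%, so completion rises from 76% to 85.6%. Suppose that 76% complete on day 5 in both arms, that the extra 9.6% in the intervention arm complete on day 25 (assumed), and that the proportion positive is the same in all groups. Under the constant hazard, initiation observed after a day-25 diagnosis is 1 − exp(−0.0554 × 5) = 24.2%. The intervention arm then shows (0.76 × 74.9 + 0.096 × 24.2)/0.856 = 69.2% against 74.9% in control, a gap of −5.7 points. With m = 2 the same mixture gives −0.7 points. The sign therefore depends on which effect dominates.

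**The case against.** Five points can be made on the other side.

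1. **The large gaps come from the constant hazard.** That model implies a mean delay of 1/0.0554 = 18 days and 96% started by day 60. It treats the 19% as slow starters, whereas Goal of the Study describes pretreatment loss as not starting treatment. If those who start do so within a few days, the gap is close to zero. This stands, and it is why no single figure can be quoted.
2. **Direction.** A reader might infer that the bias favours the interventions. The documents do not support that: late completers recovered by a reminder have short windows, as the mixture calculation shows.
3. **The date of diagnosis is not pinned down.** If it is the laboratory result date and not the participant's receipt of it, the second and third reminders, sent only once results are ready, cannot move the clock. Some participants might also have a result dated on the visit day and so a nearly full window. This could shrink the difference between arms, but it does not align the two clocks for anyone whose result comes later.
4. **Contacts may run past day 30.** Interviews take place after 30 days, with home visits and then telephone calls for those not reached, and the treatment registration date is recorded. A reader might infer that every start after day 30 is coded as a failure. The article does not say so, and a start before a late contact could be counted. Such lateness is unplanned and uneven, so it fills the window only in part.
5. **It is a secondary outcome and can be repaired retrospectively.** Both are true. They limit the weight of the point but do not remove it.

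**Conclusion.** The point holds as a mismatch between definition and schedule. On the stated timetable, treatment initiation cannot be fully observed as defined for anyone diagnosed after recruitment. If diagnosis means receipt of results, that is every diagnosed participant. Starts after the follow-up contact but within 30 days of diagnosis are missed.

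Bias between arms follows only if time to diagnosis differs by arm, and its sign is not determined. For diagnosis on day 14 versus day 5 and a true 81% in both arms, the gap is about 0 to 16 points depending on how quickly people start. Wider differences in diagnosis day give more, up to about 29 points for day 20 versus day 7 under the constant hazard. All these figures rest on assumed diagnosis days and delay distributions, so they show what is possible and do not estimate what will happen. A claim that the trial will show a large false benefit would go beyond the documents.

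**What to change.** Keep the definition of 30 days from diagnosis, and make three changes.

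1. State which date counts as diagnosis: the laboratory result or the participant's receipt of it.
2. Ascertain treatment start from the unit TB register up to 30 days after each diagnosed participant's own diagnosis date. One look-up at day 60 after recruitment covers every diagnosis made by day 30 (30 + 30 = 60). Use the TB registration number where one was collected. Participants not yet registered at the follow-up contact will not have one and must be matched on other recorded details.
3. Report that treatment registered at another facility would not be found this way.

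If the look-up is not possible, redefine the outcome as diagnosed and started on treatment within 30 days of randomisation, with all randomised participants as the denominator. Changing the time origin while keeping diagnosed participants as the denominator would leave the same truncation. The redefined outcome answers a different question, because it combines diagnosis and initiation.

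The cost is small: no new visit, and register abstraction for diagnosed participants only. At an assumed 5% to 15% positivity among 2389 recruited, that is at most about 119 to 358 people. It can be done retrospectively for those already followed up.

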Uganda’s TB burden has persisted over the years, and the country is still ranked among the 30 countries in Africa with a high burden of both TB and HIV, with an incidence of 198 cases per 100,000 population [1]. Recent studies from Uganda have reported prediagnosis LTFU of up to 40% [20] and pretreatment LTFU of 19% [21]. Diagnosis and initiation of TB treatment are critical for controlling TB transmission and achieving good patient outcomes, particularly when medication adherence is maintained [2]. Therefore, this situation calls for bold actions and innovations to reduce the number of patients lost to follow-up before completing TB diagnosis (prediagnosis LTFU) and those lost to follow-up before initiating treatment when diagnosed (pretreatment LTFU). In Uganda, mHealth interventions have emerged as promising tools to enhance TB care by improving patient outcomes and health care processes. These mHealth interventions have been used to address challenges in TB care, including contact investigation, delivery of test results, adherence to appointments, linkage to care, and treatment adherence [6,22].

The consequences of prediagnosis and pretreatment LTFU are serious. Patients with untreated TB remain infectious and can transmit TB to others, while failure to initiate treatment contributes to increased morbidity and mortality [23-26]. Therefore, monitoring the outcomes of persons with presumed TB is an important aspect of TB control [5]. This study will thus assess the effect of SMS reminders, telephone calls, and transport incentives on enhancing completion of TB diagnosis and initiation of treatment in Uganda. Assessing the effect of these interventions will provide evidence on whether reminding patients using SMS reminders or telephone calls, with or without conditional cash incentives, can enhance completion of TB diagnosis and initiation of treatment for improved patient outcomes and hence aid in designing targeted interventions and policies.

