### Objectives and Hypothesis

The primary objective is to assess the effect of SMS reminders, telephone calls, and transport incentives on completion of TB diagnosis among persons with presumed TB and initiation of treatment for diagnosed patients. The secondary objectives are to determine the median turnaround time for TB diagnosis and treatment initiation and to examine the acceptability and feasibility of the interventions. We hypothesize that compared to standard of care (SOC), each individual intervention—SMS reminders alone or telephone calls alone—will improve completion of TB diagnosis and initiation of treatment by reducing prediagnosis LTFU by a minimum of 40% (from 24% to 14.4%), while a combined intervention—SMS reminders or telephone calls coupled with transport incentives—will reduce prediagnosis LTFU by 50% (from 24% to 12%). This protocol follows the SPIRIT (Standard Protocol Items: Recommendations for Interventional Trials) reporting guidelines [27].

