### Data Management and Analysis

#### Overview

ODK data will be downloaded into Microsoft Excel and transferred to Stata 14 (StataCorp LLC) for cleaning and analysis. The primary analytical approach will follow the intention-to-treat principle, with participants in the intervention arm considered exposed to the intervention regardless of whether they received specific intervention services. We will assess for any contamination by conducting and comparing the results of the intention-to-treat and per-protocol analyses. Descriptive statistics (means, medians, and proportions) will be used to describe participant characteristics across the study arms. We will control for characteristics that are not balanced across the study arms in the fitted regression models. Chi-square tests will be performed for categorical outcomes. Log-binomial regression models using generalized linear modeling will be applied to assess associations between each intervention and the outcomes. A *P* value <.05 will be considered statistically significant.

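### Treatment initiation is compared between arms only among participants diagnosed with TB, a group formed after randomisation that the interventions are meant to enlarge, so the ratio can understate or even reverse a real gain

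*Protocol article*

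**What the plan says.** In the Protocol article, the section Trial End Points, Outcomes, and Timelines lists treatment initiation as the first secondary outcome. It requires a start within 30 days of diagnosis, and its measure is given in these words: "proportion of patients diagnosed with TB who initiated treatment out of the total number of patients diagnosed with TB recruited into the study". The primary outcome in the same section has a different denominator: the "proportion of patients who completed TB diagnosis within 30 days out of all persons with presumed TB recruited into the study".

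Other sections bear on this:

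- **Abstract, Methods:** modified Poisson models are planned for the effects of the interventions on both outcomes. The Overview under Data Management and Analysis also applies regression (there log-binomial) to the outcomes.
- **Study Population:** the trial enrols "persons with presumed TB who did not complete diagnosis on the same day as their health facility visit".
- **Objectives and Hypothesis:** prediagnosis loss to follow-up (LTFU) is expected to fall from 24% to 14.4% with SMS or calls alone, and to 12% when a transport incentive is added.
- **SMS Reminders Only and Telephone Calls Only:** the third contact also prompts participants to start treatment.

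The article gives no measure of treatment initiation over all recruited participants.

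**The concern.** Participants are randomised before diagnosis is complete, and the trial's hypothesis is that the interventions bring more of them through it. The denominator of the treatment-initiation measure is thus itself affected by the arm. The people added to it in the intervention arms are those who would otherwise have been lost, and they may well be less ready to start treatment than those who complete without help.

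Randomisation does not protect a comparison restricted to this group. The ratio combines two things: whether a given patient becomes more likely to start treatment, and which patients are counted. An arm that gets more people onto treatment could be reported as having no effect on treatment initiation, or as worsening it. The denominator is stated outright and an effect estimate is planned on it, so this is not a detail left to an analysis plan.

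**Working it through.** **The plan's own figures.** 24% × (1 − 0.40) = 14.4% and 24% × (1 − 0.50) = 12%, as stated. Completion is therefore 76% under standard of care (SOC), 85.6% with a single intervention and 88% with a combined one. Relative to SOC, the group completing diagnosis grows by 85.6/76 − 1 = 12.6% or 88/76 − 1 = 15.8%.

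**Other inputs**

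- Initiation among those diagnosed in any case: 81%, from the 19% pretreatment LTFU in the Background section (100 − 19). This is a background figure, not a design input.
- Initiation among the extra diagnosed, *p*: not in the documents. Assumed 60% to 75%.
- Assumptions: completion stands for diagnosis, the 24% loss applies equally to participants who have TB, and the interventions do not change initiation among those diagnosed anyway.

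**Formulas**, with *q* the share diagnosed in the intervention arm:

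- Started treatment, per randomised person with TB: *T* = 0.76 × 0.81 + (*q* − 0.76) × *p*
- Planned measure, among the diagnosed: *T* / *q*

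For SOC, *T* = 0.76 × 0.81 = 0.6156 (61.6%) and the planned measure is 81.0%.

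| Arm | *p* | *T* | Planned measure |
|---|---|---|---|
| Single, *q* = 0.856 | 60% | 0.6156 + 0.0576 = 0.6732 | 0.6732/0.856 = 78.6% |
| Single, *q* = 0.856 | 75% | 0.6156 + 0.0720 = 0.6876 | 0.6876/0.856 = 80.3% |
| Combined, *q* = 0.88 | 60% | 0.6156 + 0.0720 = 0.6876 | 0.6876/0.88 = 78.1% |
| Combined, *q* = 0.88 | 75% | 0.6156 + 0.0900 = 0.7056 | 0.7056/0.88 = 80.2% |

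For a single intervention the planned measure is 2.4 to 0.7 points below SOC, while the share of persons with TB who are treated rises from 61.6% to between 67.3% and 68.8%. The corresponding ratios to SOC are 0.786/0.81 = 0.97 to 0.803/0.81 = 0.99 on the planned measure, and 0.6732/0.6156 = 1.09 to 0.6876/0.6156 = 1.12 over all randomised.

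**Sensitivity to a direct effect.** If the reminders raise initiation among those diagnosed anyway by *d*, the planned measure falls below 81% only when *p* < 0.81 − 0.76 × *d* / (*q* − 0.76).

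- *d* = 2 points: *p* below 0.81 − 0.0152/0.096 = 65% (single) or 0.81 − 0.0152/0.12 = 68% (combined).
- *d* = 5 points: *p* below 0.81 − 0.038/0.096 = 41% (single) or 0.81 − 0.038/0.12 = 49% (combined).

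For example, with *d* = 2 points and *p* = 75% in a single-intervention arm, the planned measure is (0.76 × 0.83 + 0.096 × 0.75)/0.856 = 82.1% against 81.0%. The sign is right, but the ratio is 1.01, whereas over all randomised it is 0.7028/0.6156 = 1.14.

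**TB prevalence.** The proportion over all randomised participants is prevalence × *T*. Randomisation balances prevalence in expectation, so it cancels from the ratio and TB status in untested participants need not be known.

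**The case against.** The strongest reply concerns what counts as diagnosed. The 76% and 85.6% are completion figures, and completion requires both submitting sputum and receiving the result. The article does not define diagnosed in that way, and its account of routine care has patients with positive results being called back, so a positive result can exist before the patient receives it. If diagnosed means a positive result on record, participants lost between result and receipt stay in the denominator as non-initiators, and reminders that bring them back would move the planned measure in the right direction. Selection then acts only through sputum submission. This stands: the illustration is an upper bound. Selection does not vanish, because both transport-incentive sections provide for participants who could not produce sputum on the first day.

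Second, the third reminder prompts treatment start directly, which can offset the reversal. This also stands, as the sensitivity check shows.

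Third, the measure answers a natural cascade question and suits the stated objective, which covers "completion of TB diagnosis among persons with presumed TB and initiation of treatment for diagnosed patients". As a description it is sound. The difficulty is using it for a between-arm effect.

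A reader might infer three stronger points that the documents do not support:

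- **A contradiction with intention to treat.** The Overview says "The primary analytical approach will follow the intention-to-treat principle" and explains this as counting participants as exposed whatever services they received. That concerns classification by assigned arm, and analysing diagnosed patients by assigned arm does not conflict with it.
- **The same fault in the turnaround medians.** The article does not say how the medians are computed or among whom, and may leave that to the analysis plan.
- **A threat to the main result.** The objective names treatment initiation alongside completion of diagnosis, but the outcome list makes it secondary, and the numerical hypotheses and sample size concern prediagnosis LTFU only.

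**Conclusion.** The point holds for the between-arm comparison of treatment initiation, a secondary outcome. As defined, it can understate or reverse a real gain. With completion standing for diagnosis, 81% initiation among those diagnosed anyway, no direct effect and 60% to 75% initiation among the extra diagnosed, a single-intervention arm would appear 0.7 to 2.4 points worse than SOC. In the same scenario it treats 5.8 to 7.2 more per 100 randomised persons with TB (67.3 − 61.6, rounded from 67.32 − 61.56 = 5.76, and 68.76 − 61.56 = 7.20).

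It would be too strong to say that the measure will have the wrong sign. That depends on an initiation rate the documents do not give, on the meaning of diagnosed, and on the size of any direct effect of the reminders. Even without a reversal, the ratio cannot separate changed behaviour from a changed denominator. The primary outcome uses all recruited participants and is unaffected.

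**What to change.** Define the between-arm comparison as diagnosed with TB and started treatment, over all randomised participants in each arm, with the same regression model as the primary outcome. Keep the proportion among diagnosed patients as a descriptive cascade figure by arm, without an effect estimate. State what counts as diagnosed.

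Fix a time window that the follow-up can observe. The outcome now runs 30 days from diagnosis, whereas Participant Follow-Up Procedures schedules the interview 30 days after recruitment, so a late diagnosis leaves part of its window unobserved. A window counted from recruitment and ending at that follow-up would need only the diagnosis and treatment dates already being collected.

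The cost is a change of wording in the analysis. The all-randomised proportion is smaller and less familiar than the cascade percentage, which is still reported. The Results section says that preliminary analyses are under way, so the change should be recorded before results by arm are known.
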